### Data collection

Data are collected through web surveys at four time points: T0, baseline immediately after recruitment; T1, baseline part 2 at gestational week 25; T2, when the infant is 3 months old; and T3, when the infant is 12 months old. The second part of the baseline questionnaire at T1 includes questions about adverse childhood experiences, breastfeeding expectations, and pregnancy reflective functioning which are sent out in a separate questionnaire later in the pregnancy as thoughts about the child is easier to relate to at this time of the pregnancy. At T2, when the child is 3 months old, mothers are also asked to record and upload a 6-min video of mother and child playing together. At T3, when the child is 12 months old, an observational assessment and a 6-min video will be collected at either a home visit or at a municipal location by a research assistant.

Data are collected through a secured online survey database (Research Electronic Data Capture (REDCap)) that is hosted at OPEN Storage, OPEN, Open Patient data Explorative Network, Odense University Hospital, Region of Southern Denmark. REDCap logs data entry and verification. Participants receive an e-mail with a direct link to the questionnaire in e-Boks, a digital mailbox system providing all Danish citizens with a private email account tied to their social security number. Danish public agencies use e-Boks as a secure platform for digital communication with citizens (see www.e-boks.com). Reminders are sent every 3 days by e-mail. If the mothers need help to fill out the questionnaire, they will receive a phone call or help from a member of the research team. Mothers receive a 200 DKK (~ 25 EUR) electronic gift card at each of the three data collections: baseline (T0 and T1), child age 3 months (T2), child age 12 months (T3), child age 24 months (T4), and child age 5 years (T5). The research team will closely monitor the data collection process. Data will be transferred to secure servers hosted by the Agency for Governmental IT Services (Statens IT). The data platform conforms to the international ISO27001 standard on how to manage information security. The trial statistician [name], the principal investigator [name], the co-PI [name], and the senior investigator [name] will have access to the full dataset. We do not collect any biological data. Any adverse events will be monitored during the intervention and reported to the PI.

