### Measures/outcomes

Socio-demographic measures assessed at T0 - T3 include mother's age, education, occupation, ethnicity, number of children, household status, housing situation, household economy, substance abuse, and breastfeeding expectations. All study measures and outcomes are presented in Table 1.

**Table 1 Tab1:** The timing of the administration of measures

		T0	T1	T2	T3	T4	T5
Parent measures							
Socio-demographic measures	Age, education, etc.	√		√	√		
Pregnancy reflective functioning	PRFQ-P		√				
Well-being	WEMWBS	**√**		√	√		
Anxiety and depression	HADS	**√**					
Overall health parent and satisfaction	Health and satisfaction	**√**		**√**	√		
Breastfeeding duration				**√**	**√**		
Education and job expectation		√			**√**		
Family budget		**√**		**√**	**√**		
Network	Confidants, support	**√**		**√**	**√**		
Worry		**√**		**√**	**√**		
Use of alcohol, drugs, and medicine use		**√**		**√**	**√**		
Smoking		**√**		**√**	**√**		
Experiences in close relationships	ECR-R	**√**					
PTSD symptoms	PTSD-8		√				
Childhood trauma questionnaire	ACE10		√				
Postnatal depression	EPDS			**√**	**√**		
Being a mother	BaM-13			√			
Parental reflective functioning	PRFQ				**√**		
Parental stress	PSS				**√**		
Anti-conception				**√**	**√**		
Experience with cross-sectional collaboration				**√**	**√**		
Child measures							
Social-emotional development	ASQ-SE2			**√**	**√**		
Child development	ASQ-3			**√**			
Bayley Scales of Infant Development	BSID-III				**√**		
Relationship measures							
Learning activities	Singing, reading				**√**		
Mother and Baby Interaction Scale	MABISC				**√**		
Coding interactive behavior (video)	CIB			**√**	**√**		
Teacher measures							
Social-emotional development	SEAM					**√**	**√**

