#### Primary outcome

The primary outcome is maternal sensitivity measured by the Coding Interactive Behavior (CIB) instrument [67] at child age 12 months. The main hypothesis is that mothers in the intervention group will have a higher level of parental sensitivity (a CIB composite) than mothers in the control group. Maternal sensitivity is a subscale of the CIB. The CIB is a global rating system for social interactions that includes 22 parent codes, 16 child codes, and 5 dyadic codes rated on a scale of 1 to 5 which can be aggregated into the following composites: sensitivity, intrusiveness, limit setting, involvement, withdrawal, compliance, dyadic reciprocity, and dyadic negative states. The CIB is coded based on a 6-min mother-infant free play interaction recorded in the home or at another location if preferred by the family. The CIB system has been validated as an assessment measure in multiple studies of mother-child interactions in both normative and high-risk populations and shows stability over time, predictive validity, and adequate psychometric properties [67–71]. Mother-infant interactions are coded by reliable coders blind to treatment allocation. The inter-coder agreement will be calculated on a 10% randomly selected subset of the sample.

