### Data analysis

The primary outcome (CIB parental sensitivity at 12 months) is tested using linear regression with robust standard errors since we are interested in the mean difference between the groups but do not expect a perfectly normal distribution of data. The treatment effect is estimated as a fixed effect using a binary indicator of treatment. A Wilcoxon rank-sum test will be used in the case of severe non-normality. Variables with indications (*p* < 0.1) of the differences between intervention and CAU groups at baseline are used as control variables. Missing data is handled using multiple imputations using all available baseline data. Secondary outcomes are analyzed following the same principles.

Additional exploratory analyses will be carried out in a mixed-effects regression framework. This allows for growth curve estimation. Two-sided tests with 0.05 significance levels are applied throughout.

In addition to the primary analysis, we will perform subgroup analyses to examine the potential differences between subsets of participants. Hence, we analyze the subgroups according to the following characteristics: primiparous or multiparous, education (high school or less versus more than high school), concern about the family (level 1/2 or level 3/4), provider (health visitor or family therapist), adult attachment style (ECR-S), initial trauma level (ACE < 3 or ACE ≥ 3), the initial level of reflective function (lowest 50% versus highest 50%), the initial level of depression or anxiety (clinical or not-clinical level), and attendance (dose).

The primary analysis will be based on the intention-to-treat (ITT) principle, aiming to include all participants in the arm they were originally allocated to irrespective of the amount of treatment received. Missing data is handled using multiple imputations using all available baseline data. Sensitivity analyses will be performed to investigate the potential impact of missing data, in particular, by using a pre-specified conservative multiple imputation strategy and a complete case analysis.

We do not expect that participants will be harmed by the study and therefore have no predefined stopping guidelines and no a priori planned interim analyses.

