When planning the study, we expected that the number of pregnant women classified with a high level of concern (concern groups 1 and 2) and low level of concern (concern groups 3 and 4) by the midwives at the initial visit would be almost equal (160 of each). During recruitment, we have noticed that it is easier to recruit pregnant women with a low level of concern, and consequently, this group is significantly larger than the group of pregnant women with a high level of concern. This is not ideal, and we have tried to accommodate the recruitment process to this. As retention rates are also higher in the group of mothers with a low level of concern, we now expect that this group may end up accounting for 2/3 of the participating mothers. We will monitor data collection on the group of women with a higher level of concern closely and offer them extra support if needed to minimize the risk of attrition within this group.

The trial has been designed in close collaboration with practice and the intervention can be implemented immediately in the usual service if found effective. The intervention is embedded in actual practice and relies on referral to existing services from the FACAM person. The intervention aims to secure that families with a need for extra support get easier access to appropriate interventions when they are supported by a FACAM person that they trust and who knows the system.

To conclude, this is a protocol for a trial aimed at assessing the effectiveness of an early and coordinated interdisciplinary intervention offered to vulnerable pregnant women and their child. We expect that the results will add to the literature on perinatal care and provide useful evidence for future planning and organization of care for vulnerable pregnant women and their families.

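### The stated imputation rule draws on baseline data, so missing 12-month CIB sensitivity is imputed without the 3-month CIB score, the only earlier measurement of the primary outcome

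*Protocol article*

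**What the plan says.** The Data analysis section gives the missing-data rule twice, once with the regression for the primary outcome and once with the intention-to-treat statement: "Missing data is handled using multiple imputations using all available baseline data". Secondary outcomes follow the same principles. No post-baseline variable is named for the imputation model.

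The endpoint is fixed under Primary outcome: "The primary outcome is maternal sensitivity measured by the Coding Interactive Behavior (CIB) instrument [67] at child age 12 months". In Table 1 the CIB row is ticked at T2 (3 months) and T3 (12 months) only. Data collection describes both recordings. At T2, "mothers are also asked to record and upload a 6-min video of mother and child playing together". At T3, "an observational assessment and a 6-min video will be collected at either a home visit or at a municipal location". Table 1 also has EPDS, WEMWBS, BaM-13, ASQ-3 and ASQ:SE-2 at T2.

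The analysis model is a linear regression with robust standard errors: "The treatment effect is estimated as a fixed effect using a binary indicator of treatment". Missing data are to be probed "by using a pre-specified conservative multiple imputation strategy and a complete case analysis". Mixed-effects growth models are listed as exploratory.

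**The concern.** CIB codes observed play between mother and infant, so it cannot exist before birth. Baseline offers concern level, socio-demographic data and self-report scales (HADS, ECR-S, ACE, PTSD-8, P-PRFQ), none of which is an observed-interaction measure. The 3-month CIB is the same instrument as the endpoint, and the Primary outcome section credits CIB with stability over time.

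Imputing from baseline data assumes that, among women alike at baseline, loss between 3 and 12 months is unrelated to how the interaction looked at 3 months. If it is related, and differently by arm, the imputed values are systematically off in one arm and the treatment effect is biased. Conditioning on the observed 3-month data would remove that part. What is at stake is mainly bias in the primary estimate. Precision is a minor matter.

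**Working it through.** **Benchmark.** The planning effect is a standardised difference of 0.33, with two-sided alpha 0.05 and 80% power. Per arm, n = 2(1.960 + 0.842)² / 0.33² = 144.1, so 145 per arm and 290 in total. This reproduces the article's 290. Bias below is read against 0.33.

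**Inputs from the article.** 160 per arm (Procedures and randomization) and 15% dropout (Sample size justification), so 160 × 0.85 = 136 observed outcomes per arm and a standard error of about √(2/136) = 0.121 SD.

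**Inputs assumed, because the article gives none.** Correlation r between 3-month and 12-month CIB, 0.3 to 0.7. Correlation of baseline data with CIB, 0.1 or 0.3. Dropout related to 3-month CIB.

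**Hand calculation.** Suppose control dropouts scored lower at 3 months than control completers, with no such gap in FACAM. Ignoring any help from baseline predictors, bias = missing fraction × r × gap in SD:

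- 0.15 × 0.4 × 0.3 = 0.018 SD (0.018/0.33 = 5%)
- 0.15 × 0.5 × 0.5 = 0.0375 SD (11%)
- 0.15 × 0.6 × 0.8 = 0.072 SD (22%)

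Controls would be imputed too high, so the estimated difference would be too small. With the pattern reversed between arms, the sign reverses.

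**Simulation.** 160 per arm, true effect 0.33, 20 imputations combined by Rubin's rules, 600 replicates per scenario. Treatment arm was in both imputation models, and 3-month CIB was available for every woman. Missingness was set at 15% for a woman with average 3-month CIB. In the one-arm scenario the log-odds of dropout in controls rose by 1 per SD lower 3-month CIB. Averaged over controls this gives about 19% missing and a dropout-completer gap of about 0.87 SD, so it is a fairly strong mechanism.

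| Baseline corr. | r | Bias, complete case | Bias, MI from baseline | Bias, MI adding 3-month CIB |
|---|---|---|---|---|
| 0.1 | 0.3 | −0.050 | −0.050 | −0.002 |
| 0.1 | 0.5 | −0.084 | −0.083 | 0.000 |
| 0.1 | 0.7 | −0.111 | −0.109 | 0.004 |
| 0.3 | 0.3 | −0.042 | −0.028 | 0.007 |
| 0.3 | 0.5 | −0.087 | −0.073 | −0.006 |
| 0.3 | 0.7 | −0.110 | −0.096 | 0.005 |

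Monte Carlo error is about 0.12/√600 = 0.005. The hand formula agrees: 0.19 × 0.87 × r gives 0.050, 0.083 and 0.116 for r = 0.3, 0.5 and 0.7, close to the complete-case column. With weak baseline predictors, imputation from baseline barely differs from complete case. With a baseline correlation of 0.3 it removes a little of the bias.

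**Equal mechanism in both arms.** When dropout depended on 3-month CIB to the same degree in both arms (log-odds 0.7 per SD), bias lay between −0.006 and 0.006 under either imputation model. That is zero within simulation error.

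**Precision.** Adding 3-month CIB in the equal-mechanism scenarios with baseline correlation 0.1 changed the mean standard error from 0.1224 to 0.1222 at r = 0.3 (about 0%) and from 0.1218 to 0.1180 at r = 0.7 (about 3%).

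**The case against.** The article does not say that only baseline data are used. It is a condensed text, and auxiliary-variable lists often sit in an analysis plan. That is a fair caution, but naming baseline data twice as the source is a stated rule, and an analysis plan that used 3-month data would depart from it.

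The planned safeguards are real but do not close the gap. The complete-case analysis is not said to use 3-month data, and in the simulation it shares the bias. The content of the conservative imputation is not given. The mixed models could use 3-month CIB but are exploratory.

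Three limits on the benefit stand in full. Women who leave before 3 months have no T2 data. Women who decline video for fear of being judged may decline both recordings. The T2 video is recorded by the mother and the T3 video collected by a research assistant, which may lower the correlation between them. The 15% covers all dropout from pregnancy onward, so the figures treat more women as recoverable than will be.

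Two stronger readings are tempting. A reader might take the Discussion's remark, "As retention rates are also higher in the group of mothers with a low level of concern", as proof that the baseline assumption fails. It is not: concern level is recorded before randomisation and is the stratification factor, so it is baseline data and the stated rule already conditions on it. A reader might also infer that imputation is pooled over arms and would dilute subgroup effects. The article does not say whether imputation is pooled or done by arm, so that criticism has no text to rest on.

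**Conclusion.** The point holds as a weakness in a stated choice. The imputation rule omits the only earlier measurement of the primary outcome, although the trial collects it, so missing-at-random must hold given baseline data alone. The possible bias is roughly 0.02 to 0.11 SD, that is 5% to 33% of the planned 0.33, or about 0.15 to 0.9 of one standard error (0.018/0.121 and 0.109/0.121).

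That range rests on assumed correlations and on dropout that depends on 3-month CIB in one arm only. Its upper end needs a strong dependence and about 19% missing in that arm. The documents do not show that such dropout will occur. A difference by arm is conceivable, since participants are unblinded and one arm receives much more contact. If the dependence is equal across arms, nothing is lost beyond a little precision. The case for change is that the safeguard costs almost nothing.

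**What to change.** Change the rule in Data analysis to multiple imputation using baseline data plus treatment arm, concern stratum, 3-month CIB sensitivity and key 3-month questionnaires (for example EPDS and WEMWBS) as auxiliary variables. State that these 3-month measures stay out of the analysis model, because they are measured after randomisation and adjusting for them could remove part of the treatment effect. Record the change before allocation is unmasked to the analysts, so that it cannot look data-driven.

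Keep the auxiliary list short. With about 136 observed primary outcomes per arm, a separate model in each arm containing every T0 to T3 variable would risk overfitting and non-convergence. Women without T2 data will have those auxiliaries imputed as well. The cost is slightly more imputation modelling; no new data are needed.

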**Methods:**

The study is a prospective randomized controlled trial where we will randomize 320 pregnant women enrolled to receive antenatal care at the family clinic at Odense University Hospital, to either FACAM intervention or usual care. The FACAM intervention consists of extra support by a health nurse or family therapist during pregnancy and until the child starts school. The intervention is most intensive in the first 12 months and also includes attachment-based support provided either individually or in groups. The participants are assessed at baseline, and when the infant is 3 and 12 months old. The primary outcome is maternal sensitivity measured by the Coding Interactive Behavior (CIB) instrument. Secondary outcomes include prenatal parental reflective functioning, mental well-being, depressive symptoms, breastfeeding duration, maternal satisfaction, child development, parent competence, parental stress, and activities with the child.

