Bayley Scales of Infant and Toddler Development 3rd Edition - Screening Test (BSID) is a standardized norm-based test widely used to assess child development (Bayley, 2006). The BSID consists of three main subtests; the Cognitive Scale, which includes items such as attention to familiar and unfamiliar objects, looking for a fallen object, and pretend play; the Language Scale, which taps understanding and expression of language, for example, recognition of objects and people, following directions, and naming objects and pictures; and the Motor Scale, which assesses gross and fine motor skills such as grasping, sitting, stacking blocks, and climbing stairs. The cognitive scale assesses memory and problem solving, exploration and manipulation, object relatedness, and sensorimotor development. Raw scores for each subscale are converted into scaled scores (range 1–19, M = 10, SD = 3), and a composite score (M = 100, SD = 15) can be derived from the scaled score for cognitive development, and the sum of the two language-scaled scores. The test will be administered at T3 by trained psychology students supervised by an experienced and trained psychologist.

The mothers will also be asked single items about overall health, life satisfaction, breastfeeding intention, breastfeeding duration, use of birth control, supportive network, loneliness, and how they experience the cross-sectional collaboration between the professionals. If the mother is not employed, she will be asked questions about the indicators for progression toward employment (belief in own skills, mastery of health, and work identity). These items were developed in the employment indicator project [84].

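### Breastfeeding duration falls under a mean-difference regression with imputation from baseline data, which leaves open what is estimated and ignores the 3-month answer of a mother who misses the 12-month survey

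*Protocol article*

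**What the plan says.** The abstract lists the outcome: "Secondary outcomes include prenatal parental reflective functioning, mental well-being, depressive symptoms, breastfeeding duration, maternal satisfaction". The Secondary outcomes section shows that it is one of several questions put to the mother, the "single items about overall health, life satisfaction, breastfeeding intention, breastfeeding duration, use of birth control". Table 1 ticks it at T2 and T3 only, and Data collection defines these as "T2, when the infant is 3 months old; and T3, when the infant is 12 months old".

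The Data analysis section sets the method for the primary outcome, which is "tested using linear regression with robust standard errors since we are interested in the mean difference between the groups", with a Wilcoxon rank-sum test if non-normality is severe. On missing values it says: "Missing data is handled using multiple imputations using all available baseline data". It then extends all of this in one sentence: "Secondary outcomes are analyzed following the same principles". The planned sensitivity analyses are a conservative multiple imputation and a complete-case analysis. Nothing is said about a duration still running at a survey, or about a 3-month answer from a mother who does not answer at 12 months.

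**The concern.** Duration is right-censored for every mother still breastfeeding when last asked. A mean-difference regression needs one finished number per woman, so something must be entered for her, and the plan does not say what. Different choices estimate different quantities.

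The second difficulty concerns dropout, which the article puts at around 15%. Among mothers who miss T3 but answered T2, some have already given an exact stopping age, so the outcome is fully known. Others were still breastfeeding at 3 months, so at least 3 months is known. Imputation described as using baseline data uses neither fact. The sensitivity analyses do not repair this: one imputes again and the other drops the woman.

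At stake is the interpretability of one secondary outcome, and the use of data that the trial has already paid to collect.

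**Working it through.** **Inputs from the article.** 320 women, 1:1; about 15% dropout; surveys at 3 and 12 months; two-sided 0.05. That gives 320 × 0.85 / 2 = 136 analysed per arm. The article states no power or expected value for breastfeeding duration, so there is no figure of its own to reproduce.

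**Assumptions (not in the article).** Exponential time to stopping; 5–30% of control mothers still breastfeeding at 12 months; hazard ratio (HR) for stopping 0.7.

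**1. What is estimated.** Let λ = −ln S(12)/12 in controls and 0.7λ in FACAM. Mean full duration is 1/λ. Mean months up to 12 is (1 − S(12))/λ. The mean among mothers who stopped by 12 months is [(1 − S(12))/λ − 12·S(12)] / (1 − S(12)).

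With S(12) = 0.10 in controls, λ = 0.1919. In FACAM, 0.7λ = 0.1343 and S(12) = 0.10^0.7 = 0.200.

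- Full duration: 7.45 − 5.21 = 2.23 months (unrounded inputs).
- Months up to 12: 5.96 − 4.69 = 1.27.
- Stopped mothers only: 4.45 − 3.88 = 0.58 (unrounded inputs).

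| Controls still breastfeeding at 12 months | Full duration | Months up to 12 | Stopped mothers only |
|---|---|---|---|
| 5% | 1.72 | 1.21 | 0.67 |
| 10% | 2.23 | 1.27 | 0.58 |
| 20% | 3.20 | 1.23 | 0.44 |
| 30% | 4.27 | 1.13 | 0.34 |

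A simulation with 400,000 durations per arm agrees with these to within about 0.03 months. The last column matters only if ongoing breastfeeding were coded as missing, because an imputation model would then learn from stopped mothers alone.

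**2. Power at 136 per arm, 10% scenario.** For months up to 12 the pooled SD is 4.0, so the standard error is 4.0 × √(2/136) = 0.485. Then 1.27/0.485 − 1.96 = 0.66, which gives about 75%. For log-rank, events are 136 × (0.90 + 0.80) = 231. Then √(231/4) × |ln 0.7| − 1.96 = 0.75, which gives 77%. At 20% and 30% still breastfeeding, the pairs (capped, log-rank) are 68% and 71%, and 59% and 65%. A comparison of stopped mothers only, as a stand-in for imputing the rest, has about 30%, 16% and 10% in the three scenarios.

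**3. The mother who misses T3.** Take one who was still breastfeeding at 3 months. If baseline variables do not predict duration, and draws follow the distribution in her arm, an imputed value falls below 3 months with probability 1 − S(12)^(3/12). In the 10% scenario this is 1 − 0.562 = 44% in controls and 1 − 0.668 = 33% in FACAM. Over the 5–30% range it is 53% down to 26% in controls and 41% down to 19% in FACAM. Predictive baseline variables would lower these figures, but nothing in the rule excludes such values.

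**4. Effect on the comparison.** Suppose 25% of mothers who stopped by 3 months miss T3, against 8% of those still breastfeeding then. In the 10% scenario overall dropout is then 15% in controls and 14% in FACAM. Mean months up to 12 are 1.36 (stopped by 3 months) and 7.29 (still breastfeeding) in controls, and 1.40 and 8.22 in FACAM. If allocation is in the imputation model, each arm's estimate equals its respondents' mean:

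- Controls: (0.438 × 0.75 × 1.36 + 0.562 × 0.92 × 7.29) / (0.438 × 0.75 + 0.562 × 0.92) = 4.98, against a true 4.69.
- FACAM: (0.332 × 0.75 × 1.40 + 0.668 × 0.92 × 8.22) / (0.332 × 0.75 + 0.668 × 0.92) = 6.26, against a true 5.96.

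Both means are about 0.3 months too high, while the difference stays at 1.27. Across the 5–30% scenarios the difference moves by at most about 3%. If allocation were left out of the imputation model, 15% dropout at random would shrink the difference to 1.27 × 0.85 = 1.08.

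**The case against.** A reader might infer more: that mothers still breastfeeding are certain to receive a wrong duration, and that the treatment effect is bound to be diluted. The article does not support that. Imputation is specified for missing data, and a mother who says she is still breastfeeding has answered. The shrinkage from 1.27 to 0.58 months, and the power of 10–30%, follow only if her answer is coded as missing, and no section says so. The shrinkage is also smaller if the intervention acts only early: with an HR of 0.6 confined to the first 3 months and 10% of controls still breastfeeding at 12 months, the difference falls from 0.88 to 0.76 months.

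Entering 12 for such a mother is legitimate. It gives the restricted mean to 12 months without bias and loses about 2–6 power points against log-rank here. Nor does the article announce a separate comparison of durations at 3 months; ticks at both visits fit a single combined variable equally well.

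It can also be said that coding belongs in an analysis plan not shown here, and that T1 collects breastfeeding expectations, which would inform the imputation. Both are fair. But the article is not silent: it assigns one method to every secondary outcome and describes imputation as drawing on baseline data. An analysis plan that handled this outcome well would have to depart from that sentence.

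**Conclusion.** The point holds in a limited form. The stated rule leaves open whether full duration or months in the first year is estimated. Under the assumed rates, that changes the reported difference from 1.72 to 1.21 months at one end of the range and from 4.27 to 1.13 at the other. Full duration cannot be observed from these surveys for mothers still breastfeeding at 12 months, so only the restricted target is directly estimable.

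Taken literally, the imputation rule also discards known 3-month answers when T3 is missed. That affects at most about 48 women (15% of 320), and fewer if some leave before T2; the article gives no split. The expected distortion of the arm difference is small if allocation is in the imputation model. The case for changing the rule is that it can contradict observed data and waste information, not that it would overturn a result.

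All sizes rest on assumed breastfeeding rates, hazard ratios and exponential durations. The primary outcome, maternal sensitivity at 12 months, is not touched.

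**What to change.** - Exempt breastfeeding duration from the sentence on secondary outcomes.
- Combine T2 and T3 into one time-to-cessation variable: an event at the reported stopping age, otherwise censoring at the child's age at the last completed survey.
- Compare arms by the difference in restricted mean breastfeeding time to 12 months, accounting for the two level-of-concern strata, with a stratified log-rank or Cox test as support. This keeps the mean-difference target the authors want.
- State that ongoing breastfeeding is an observed answer and is never imputed.

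The cost is a few sentences and a standard survival routine on data already collected. There are two drawbacks. The estimate is limited to the first 12 months and must be labelled so. Censoring at T2 assumes that dropout is non-informative given stratum, and the Discussion reports better retention among mothers with a low level of concern, which is why the strata should enter the main comparison. Multiple imputation that uses T2 as well as baseline data, constrained to respect what T2 established, can serve as the sensitivity analysis. The choice should be fixed before allocation is revealed to the analysts.
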